## Abstract

**Introduction:** Treatment of autoimmune pancreatitis (AIP) is based solely on consensus and has yet to become standardized. Consequently, therapeutic regimens vary greatly between countries and centers, and largely depend on the experience of the physician. At this moment, the optimal regimen for inducing disease remission and preventing relapse is unknown.

**Objectives:** The primary objective of this study is to describe current treatment regimens used in Europe, and to compare their effectiveness in inducing remission and preventing and treating relapse. The secondary objectives are: to identify risk factors for relapse; to assess the diagnostic accuracy of the Unified-AIP criteria; to assess the performance of the M-ANNHEIM score for predicting relapse; and to assess long-term outcomes including pancreatic exocrine insufficiency and pancreatic cancer.

**Methods:** This is an international, retrospective, observational cohort study, performed in over 40 centers from 16 European countries. Eligible are all patients diagnosed with AIP from 2005 onwards, regardless of the used diagnostic criteria. Data on study subjects will be retrieved from the hospital's electronic medical records and registered with a standardized, web-based, electronic case report form (eCRF). To compare the effectiveness of treatment regimens in inducing remission, preventing relapse, and treating relapse, subjects will be stratified in groups based on: type of therapy; initial therapy dose; cumulative therapy dose; therapy tapering speed and duration; and having received maintenance therapy or not.

**Ethics and Dissemination:** Ethical and/or institutional review board approvals are obtained by all participating centers according to local regulations. The study complies with the General Data Protection Regulation (GDPR). All manuscripts resulting from the study will be submitted to peer-reviewed journals.

**Conclusion:** This is the first pan-European retrospective registry for AIP. It will produce the first large-scale data on treatment of European patients with AIP, providing answers on the use and effectiveness of treatment regimens. In the future, this collaboration may provide a network for continuation into a prospective European registry.

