All AIP subtypes respond dramatically to steroid treatment (up to 99% in the different cohorts) (11–14), but the optimal dose to induce remission remains controversial. Reported induction doses have ranges between 30 and 60 mg daily (11–14) Recently, other therapeutic options, that induce B-cell depletion, have also been employed in inducing AIP remission, with promising results (15, 16). In a cohort from France, the reported efficacy was 94% with two infusions given in most patients (17). However, in spite of the dramatic response to initial treatment, the risk of relapse within 1 year from disease remission ranges between 30 and 50% (12), being higher in type 1 than in type 2 AIP patients (12). Several risk factors for AIP relapse have been proposed, but have not been validated prospectively (11, 12, 18, 19). Due to the high frequency of relapse after induction, some authors recommend maintenance treatment with low-dose steroids or immunomodulators, but the patient group that would benefit from maintenance is currently unknown (20–26).

Thus far, data on the epidemiology and natural history of AIP are still scant due to its rarity and its relatively recent appraisal. Most of the data comes from Asian or North-American cohorts, while data on large European cohorts are lacking. As a consequence, treatment options applied in Europe are largely based on retrospective studies from Asian and North-American patients.

We established the PrescrAIP (A Pan-European Study on Current Treatment Regimens of Auto-immune Pancreatitis) study network to retrospectively describe the current status of AIP treatment in Europe on a large scale. In addition, our effort will create the opportunity for a subsequent international prospective registry that will be able to provide definite answers in the future. In particular, in this retrospective multicentre study, we aim to define and compare the AIP treatment regimens used throughout different European centers, highlighting their differential impact on disease remission and long-term outcomes. These results will foster our knowledge of this rare disease, yielding to better patient care.

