### Assessment Variables

At the time of inclusion, all relevant variables will be recorded in the eCRF. These will include variables on demography and epidemiology, disease characteristics (radiological, laboratory and clinical), the set of diagnostic criteria employed, treatment (type, dose, duration), and short and long-term clinical outcomes. The complete variable list and definitions are reported in Appendix 1. AIP subtypes will be defined following the analysis of the above-mentioned variables. Given that patients with elevated serum IgG4 but without other organ involvement or biopsy sample can potentially be misdiagnosed, a subgroup with these characteristics will be created. Then a sensitivity analysis with and without excluding this subgroup will be performed to evaluate potential differences in the outcomes.

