### Study Endpoints

Our primary endpoints consist of remission of disease (defined as the absence of clinical symptoms and the resolution of pancreatic abnormalities on imaging), relapse of disease, relapse rates compared between patients with a low or a high dose regimen, cumulative maintenance therapy dose and relapse-free survival time. Our secondary study endpoints are gold standard diagnostic tools of AIP compared to U-AIP, the prevalence of pancreatic exocrine insufficiency and the cumulative incidence of pancreatic ductal adenocarcinoma. The diagnosis of diabetes mellitus [as defined by the American Diabetes Association (27)] either before or after steroid treatment is our tertiary study endpoint.

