### Statistical Analysis

Continuous, non-normally distributed values will be presented as median and interquartile range (IQR), unless otherwise specified. Discrete variables will be presented as frequency (percentage). Normal distribution of continuous variables will be assessed with the Kolmogorov–Smirnov algorithm. Normally distributed variables among the different groups will be compared using the Student's *t*-test. Non-normally distributed variables will be compared using the Mann–Whitney *U*-test. Categorical variables will be analyzed by the Fisher's exact test or chi-square test.

To compare remission rates, relapse rates, relapse-free survival and long-term outcomes between participants, we will stratify participants according to the date of diagnosis, meeting the different diagnostic criteria, the type of treatment, the glucocorticoids starting dose, the cumulative dose, tapering speed, and treatment with maintenance treatment.

Moreover, to assess the impact of the treatment effect being part of the diagnostic criteria, we will perform sensitivity analyses comparing the study outcomes between those classified as AIP regardless of the steroid trial, and those in whom the diagnosis was dependent on the steroid trial. Sensitivity analyses will also be performed to compare the study outcomes including or excluding individuals that do not meet any available diagnostic criteria, and those classified as NOS-AIP.

Kaplan-Meier curves will be used to assess time-to-relapse. Time-to-relapse will be compared between subgroups using the log-rank test. Univariable and multivariable analyses with a backward selection procedure will be performed to identify possible predictors for relapse, based on a Cox-proportional hazards regression model. A significance threshold of *P* < 0.05 will be used.

Data from national pancreatic cancer registries will be used to determine age- and sex-specific incidence rates for pancreatic ductal adenocarcinoma. Standardized incidence ratios (SIRs) will be then calculated by obtaining the ratio of the observed to the expected number of cases, and 95% confidence intervals (95% CIs).

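### The primary dose comparison splits dose into low and high, and no continuous dose-response analysis is described; the split hides shape and usually costs precision, by an amount the article does not fix

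*Protocol article*

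**What the plan says.** Study Endpoints names "relapse rates compared between patients with a low or a high dose regimen" as one of the primary endpoints.

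The Statistical Analysis section compares remission rates, relapse rates, relapse-free survival and long-term outcomes by stratifying patients on, among other things, "the glucocorticoids starting dose, the cumulative dose, tapering speed, and treatment with maintenance treatment". The Abstract describes the same approach: "subjects will be stratified in groups based on: type of therapy; initial therapy dose; cumulative therapy dose; therapy tapering speed and duration". For the time-to-event outcome the named method is a group comparison: "Time-to-relapse will be compared between subgroups using the log-rank test".

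A regression model is also planned: "Univariable and multivariable analyses with a backward selection procedure will be performed to identify possible predictors for relapse", using Cox regression. The article does not say whether dose enters that model, or in what form.

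Under Assessment Variables, the recorded data include "treatment (type, dose, duration" of treatment. As background, the Introduction says: "Reported induction doses have ranges between 30 and 60 mg daily". No cut-point, number of strata, cohort dose distribution, sample size or power figure appears in the article. Variable definitions are referred to Appendix 1.

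**The concern.** The Discussion says that the best starting dose and tapering speed are still unclear, and the Introduction calls the induction dose controversial. Answering that calls for a description of how relapse and remission change across the doses actually given. A low/high contrast yields one difference. It treats patients just below and just above the cut as different and patients at the two ends of one group as alike. It cannot separate a steady gradient from a plateau or a threshold, and moving the cut can change the result.

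This is more than a missing cut-off. A definition in Appendix 1 would say where the split lies, but the split would remain the primary dose endpoint. At stake are the precision of the main dose comparison and whether the study can inform the dose question it raises.

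**Working it through.** The article states no power or sample size, so there is no figure of its own to reproduce. The check asks how much information about a linear dose effect survives grouping.

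**Inputs.** From the article: a two-group primary contrast (Study Endpoints), a background range of 30-60 mg daily (Introduction) and a 0.05 significance threshold (Statistical Analysis). Assumed: a two-sided test, the dose distributions below, and that the low/high regimen refers to starting dose.

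**Measure.** Information kept, R, is the squared correlation between dose and its grouped version. The loss is 1 − R.

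**Smooth dose, share p in one group.**
- Uniform: R = 3p(1−p). At p = 0.5, R = 0.75, loss 25%. At p = 0.2, R = 3 × 0.16 = 0.48, loss 52%.
- Normal: R = φ(z_p)²/[p(1−p)]. At p = 0.5, R = 2/π = 0.637, loss 36%. At p = 0.2, R = 0.490, loss 51%.

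**Clustered doses.** Take 30, 40 and 60 mg as equally frequent. The mean is 43.3 and the variance 155.6. A split into one third and two thirds has variance 2/9 = 0.222.
- 40 mg and above called high: covariance 4.44, R = 4.44²/(155.6 × 0.222) = 0.571, loss 43%.
- Only 60 mg called high: covariance 5.56, R = 5.56²/(155.6 × 0.222) = 0.893, loss 11%.
- If only two doses occur, R = 1 and the loss is 0%.

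Less even cases are worse. Weights of 0.2/0.6/0.2 on 30/40/60 mg with the cut at 40 lose 62.5%, and weights of 0.1/0.8/0.1 lose 73%. A lognormal cumulative dose split at its median loses 41-63% for a log-SD of 0.3-0.8.

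**More than two strata, equal groups.**

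| Groups | Loss, normal | Loss, uniform |
|---|---|---|
| 3 | 20.7% | 11.1% |
| 4 | 13.9% | 6.2% |
| 5 | 10.3% | 4.0% |

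**Power.** If a one-degree-of-freedom linear dose test has 80% power, its standardised effect is 1.96 + 0.84 = 2.80. After the split, power = Φ(2.80√R − 1.96).
- R = 0.75: 68%
- R = 0.637: 61%
- R = 0.49: 50%

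**Power of a spline test.** For the same linear effect the noncentrality is 2.80² ≈ 7.85. The overall test of a 3-knot spline (2 degrees of freedom) has 71% power, and that of a 4-knot spline (3 degrees of freedom) has 64%.

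**The case against.** The strongest reply is that the loss may be small. Prescribed doses may sit at a few values, the 30-60 mg range comes from the literature and not from this cohort, and Study Endpoints speaks of a dose regimen without saying that this means starting dose. With two doses in use, nothing is lost. This stands. A reader might infer that the split discards a fixed quarter to a half of the dose information; the article does not support that, because the figure rests on a smooth distribution and a cut that is not extreme.

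A reader might also extend the two-group loss to cumulative dose and tapering speed. The number of strata is not stated, and three or more strata lose much less and still show a coarse shape.

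Nor does the article say that dose is handled only by grouping. It leaves open how dose enters the Cox model, so a claim that grouping weakens adjustment for dose there is unsupported. The general two-sample tests could also compare undivided dose between patients with and without relapse. Neither route replaces the primary contrast. The Cox model is described as a backward-selection search, from which dose could be dropped, and it covers relapse and not remission. A two-sample test of dose does not give relapse risk as a function of dose.

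The power argument favours a single dose term, not splines in general. At 71% or 64%, an overall spline test is little better than a median split at 68% or 61%. If the true effect is a threshold near the cut, a split can be efficient.

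Finally, knots and covariate coding usually belong in an analysis plan, and the Discussion calls the study descriptive. Those details are indeed not missing here. But the low/high contrast is a stated choice, and the primary objective includes comparing the effectiveness of regimens.

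**Conclusion.** The point holds in limited form. The article fixes a two-group dose contrast as a primary endpoint, groups the related exposures, and describes no continuous dose-response analysis although the data appear to allow one. The loss of shape and the dependence on the cut follow from the two-group method wherever the cut lies, unless only two doses occur.

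The loss of precision is likely but its size is unknown. For a linear effect and a two-group split, it runs from 0% to about 51-52% over the main scenarios (only two doses, three equally frequent doses, and a median or 80/20 cut of a smooth distribution). It is higher with extreme cuts, strong clustering or marked skew. All these figures rest on assumed distributions and should be quoted as a range. The change is worth making, because it suits the study's own dose question and needs little.

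**What to change.** Make regression models the main dose analyses: Cox for relapse and logistic for remission. Enter starting dose, cumulative dose and tapering speed as prespecified continuous terms that are kept in the model and not subject to backward selection. Test each with a single linear or log-dose term. Where the dose values support it, add a restricted cubic spline with few knots to describe shape and check non-linearity; if only a few distinct doses occur, the spline adds little. Keep the low/high groups and the strata for descriptive tables and Kaplan-Meier plots.

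The cost is analysis wording and a few model terms. Dose and duration are already recorded, so no new data appear to be needed. The downside is that a curve is less simple to report than one contrast, which is why the groups stay as a display. The change concerns the form of the dose variables only and does not deal with confounding between dose and disease severity.

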## Introduction

Autoimmune pancreatitis (AIP) has recently been recognized as an immune-mediated disease of the pancreas with distinct features (1). It is a rare disease with an annual incidence of ~3.1/100,000, which varies substantially between geographical regions (2). To date, two types of autoimmune pancreatitis have been described (1). Type 1 AIP is the pancreatic manifestation of IgG4-related disease (IgG4-RD). It shares clinical and histological hallmarks with IgG4-RD, namely increased serum Immunoglobulin G4 (IgG4) levels, dense storiform fibrosis, and IgG4-positive plasma cell infiltration of the affected organ (3). Type 2 AIP is known as idiopathic duct-centric pancreatitis and is characterized by neutrophil-mediated duct destruction, in the form of granulocytic epithelial lesions (GEL) (4). Both types can cause abdominal pain and jaundice and can ultimately lead to chronic pancreatitis (1). This in turn, might even increase the risk of developing pancreatic cancer (5). Yet, the incidence of these complications has not been clearly established.

In the last two decades, several efforts have been made to establish diagnostic criteria (1, 6–8), which are all based on the combination of clinical, serological, and pathological features. Nevertheless, AIP cases are still missed or even mistaken for pancreatic ductal adenocarcinoma (9, 10). As such, sequelae of chronic pancreatitis with endocrine and exocrine insufficiency can develop or the diagnosis of type 1 and type 2 AIP is made after unnecessary surgery (11). In addition, a discrete percentage of AIP cases does not fulfill diagnostic criteria for type 1 or type 2 AIP and thus are referred to as Not-Otherwise-Specified (NOS) AIP (1).

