## Objectives

The primary objective of this study is to describe AIP treatment regimens across Europe, and to compare the effectiveness of treatment regimens in inducing remission, preventing and treating relapse. The secondary objectives include identifying risk factors for relapse, assessing the diagnostic accuracy of the U-AIP criteria (6), assessing the performance of the M-ANNHEIM score for predicting relapse (19), and assessing long-term outcomes including pancreatic exocrine insufficiency and pancreatic cancer. Thirdly, we are aiming to assess whether standard treatment was altered due to pre-existing diabetes mellitus, determine the prevalence of diabetes mellitus before and after steroid treatment, assess glycemic control in patients with diabetes mellitus and to describe the clinical, radiological and pathological characteristics of a cohort of patients diagnosed with AIP through pancreatic resection.

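### Exocrine insufficiency is measured as undated prevalence, which suits a description of burden but not the planned non-randomised regimen comparison, because it includes cases present before treatment

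*Protocol article*

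**What the plan says.** The Objectives section of the protocol article makes exocrine insufficiency part of a secondary aim: "assessing long-term outcomes including pancreatic exocrine insufficiency and pancreatic cancer". Study Endpoints then fixes the measures: "the prevalence of pancreatic exocrine insufficiency and the cumulative incidence of pancreatic ductal adenocarcinoma". The cancer endpoint is an incidence. The insufficiency endpoint is a prevalence with no time point. The tertiary endpoint, a diagnosis of diabetes, is tied to treatment: "either before or after steroid treatment is our tertiary study endpoint".

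The Statistical Analysis section says how outcomes will be compared: "To compare remission rates, relapse rates, relapse-free survival and long-term outcomes between participants, we will stratify participants according to the date of diagnosis", then by diagnostic criteria met, then by "the type of treatment, the glucocorticoids starting dose, the cumulative dose, tapering speed, and treatment with maintenance treatment". Categorical variables are compared by Fisher's exact or chi-square test. The only multivariable model described is the Cox model for predictors of relapse.

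On the origin of insufficiency, the Introduction says of missed or mistaken cases that "sequelae of chronic pancreatitis with endocrine and exocrine insufficiency can develop". On definitions, Assessment Variables says: "The complete variable list and definitions are reported in Appendix 1". That appendix is not part of the text at hand.

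**The concern.** A regimen can only influence insufficiency that arises, persists or resolves after it begins. An undated prevalence also takes in patients who already had the condition. The Introduction allows for such patients, since insufficiency can develop while the disease goes unrecognised.

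Regimens here were not randomised, and the Abstract says that they vary by country, center and physician. Nothing therefore guarantees that pre-treatment insufficiency is balanced between the groups compared. Imbalance moves the comparison even when regimens do not differ in effect, and balance dilutes a true difference. Both would happen with identical follow-up in every group, so this problem is separate from unequal follow-up.

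At stake is the reading of one secondary endpoint in the regimen comparisons. The primary analyses of remission and relapse are not touched.

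**Working it through.** The article gives no rate of exocrine insufficiency, no sample size and no power figure, so there is nothing of its own to reproduce. The check has two parts.

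**1. The text, side by side**

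| Outcome | Measure in Study Endpoints | Tied to treatment or to new events? |
|---|---|---|
| Pancreatic ductal adenocarcinoma | Cumulative incidence | Yes, new events |
| Diabetes mellitus | Diagnosis before or after steroids | Yes, treatment |
| Exocrine insufficiency | Prevalence | Neither |

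Insufficiency is a long-term outcome (Objectives), and long-term outcomes are compared by regimen (Statistical Analysis). The tests named for categorical outcomes do not use baseline status. The planned sensitivity analyses concern certainty of diagnosis and subtype, not baseline insufficiency.

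**2. Illustration (all inputs assumed)**

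Let b be the share with insufficiency before treatment and q the risk of new insufficiency among the rest. If every pre-treatment case is still counted,

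prevalence = b + (1 − b)q.

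*No regimen effect (same q in groups A and B).* The difference is (b_B − b_A)(1 − q). With p_A and p_B the two prevalences, d their difference, p̄ their mean and n = 100 per group (assumed), the chance of a two-sided P < 0.05 is about Φ[(|d| − 1.96·SE0)/SE1]. Here SE0 = √(2p̄(1 − p̄)/n) and SE1 = √([p_A(1 − p_A) + p_B(1 − p_B)]/n).

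| b_A vs b_B | q | Prevalence A vs B | Difference (points) | Chance of P < 0.05 |
|---|---|---|---|---|
| Equal | 10% or 20% | Equal | 0 | 5% |
| 10% vs 20% | 10% | 19% vs 28% | 9 | 32% |
| 10% vs 20% | 20% | 28% vs 36% | 8 | 23% |
| 20% vs 40% | 10% | 28% vs 46% | 18 | 75% |
| 20% vs 40% | 20% | 36% vs 52% | 16 | 63% |
| 30% vs 50% | 10% | 37% vs 55% | 18 | 73% |
| 30% vs 50% | 20% | 44% vs 60% | 16 | 62% |

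Second row: 0.10 + 0.90 × 0.10 = 0.19 and 0.20 + 0.80 × 0.10 = 0.28.

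*True doubling of new onset (q = 10% vs 20%), equal b.* The difference is (1 − b)(q_B − q_A).

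| b | Prevalence A vs B | Ratio | Share of A's cases present before treatment |
|---|---|---|---|
| 0% | 10% vs 20% | 2.00 | 0% |
| 10% | 19% vs 28% | 1.47 | 53% |
| 20% | 28% vs 36% | 1.29 | 71% |
| 30% | 37% vs 44% | 1.19 | 81% |
| 40% | 46% vs 52% | 1.13 | 87% |

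Comparing q directly, among patients free of insufficiency at treatment start, returns a ratio of 1.0 in the first table and 2.0 in the second, whatever b is.

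*If some cases resolve.* If a share r of pre-treatment cases has resolved when prevalence is read, b is replaced by b(1 − r) in the first term. The spurious difference becomes (b_B − b_A)(1 − r − q), which is smaller as long as r + q stays below 1. The tables take r = 0.

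**The case against.** The best defence is that the article is silent on timing and does not positively pool old and new cases. Appendix 1 may record insufficiency at diagnosis, or its date of onset, and a condensed article may leave time anchors to such a document. The authors also use prevalence for a time-indexed quantity when they plan diabetes prevalence before and after steroids. This part stands: the data for a better measure may already exist. It does not remove the point, because the endpoint as worded uses none of that information and feeds a comparison by regimen.

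Second, the effectiveness objective concerns remission and relapse, the Discussion calls the study descriptive, and prevalence measures burden well. This also stands for description. It does not cover the Statistical Analysis section, which puts long-term outcomes in the same stratified comparison as remission and relapse.

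Third, the diabetes split serves its own tertiary question. That is fair: the contrast shows that the split is feasible and familiar to the authors, not that its absence here was an oversight.

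Fourth, a regimen given to patients with more pancreatic damage may show more new insufficiency too, so restricting to unaffected patients is only a partial cure. This is correct. The illustration leaves it out by giving both groups the same q in the no-effect case.

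A reader might infer that pre-treatment insufficiency will be attributed to the regimen, or that a regimen favoured in more damaged pancreata is bound to look harmful. The article supports neither. It makes no causal claim about insufficiency, reports no imbalance between regimens, and says only that insufficiency can develop in missed cases, not how often.

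**Conclusion.** The point holds in a limited form. Undated prevalence is acceptable for describing burden and poorly suited to the regimen comparison that the article plans for long-term outcomes. In that comparison it can create a difference when pre-treatment insufficiency is unbalanced, and it dilutes one when it is balanced.

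The size is unknown. Over the assumed ranges, an imbalance of 10 to 20 points produces a spurious difference of 8 to 18 points, and a true doubling shrinks to a ratio between 1.47 and 1.13. With balanced baselines and no regimen effect, the error is zero. These figures rest on assumed rates, 100 patients per group and no resolution of pre-treatment cases. They show direction and mechanism and are not estimates for this cohort. In particular, a reader should not infer that most counted cases in this study predate treatment: the article offers no figure for that.

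It concerns one secondary endpoint, can be corrected cheaply, and is worth settling before the regimen comparisons are run.

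**What to change.** Divide the endpoint at the start of first treatment:

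- **Descriptive:** prevalence of exocrine insufficiency at diagnosis and at last follow-up.
- **For regimen comparisons:** new exocrine insufficiency after the start of first treatment, among patients without it at that time. This parallels the before/after split already used for diabetes.
- **Descriptive:** persistence or resolution among patients affected at treatment start.
- **Unknown baseline status:** shown as a separate group, not counted as unaffected.

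State regimen results for this outcome as associations, since confounding by indication remains after the split.

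The cost is a change of endpoint wording and, unless Appendix 1 already provides it, a chart date for first diagnosis of insufficiency or start of enzyme replacement. There are two downsides. The comparison set becomes smaller, and dating onset retrospectively from records in 44 centers will be imperfect, so some patients will be placed on the wrong side of treatment start.
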